### Data analysis

Patient eligibility, recruitment and retention through the study will be presented in a CONSORT flow diagram displaying the number of eligible patients, patients approached with study information, patients recruited and randomised and patients completing study follow-up. Reasons for loss to follow-up will also be presented, where known. Participant baseline details and descriptive statistical data will be tabulated to show overall recruit demographics, and any differences in distribution (e.g. patient age, sex, level of education) will be analysed by applying one-way ANOVA or chi-squared test.

The primary outcome, the degree of difference in patient knowledge about their glaucoma condition will be analysed by comparing the average scores for control patients versus the average score of patients received the glaucoma personal record. Statistical significance will be assessed by applying the Mann–Whitney *U* test. The secondary outcome, visual field loss, will be measured with a Humphrey Automated Visual Field Analyser in the ophthalmology clinic and average measurements for baseline visit and the final visit at 36 months will be compared within each group (control and intervention respectively) and also between the two groups. Depending on distribution of the data, determined by Shapiro-Wilk test, the paired *t* test or Wilcoxon test will be applied for paired samples to determine any significant changes in visual field loss. For assessing differences between the control and intervention groups, either *t* test or Mann–Whitney *U* test will be applied. Like visual field loss, the other secondary outcome measure - patient-related outcome measure VFQ-25 - will be presented as average scores. Any statistical differences will be assessed by Wilcoxon test within each group and Mann–Whitney *U* test between groups.

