**Methods/Design:**

HOPE Glaucoma is a 3-year, prospective, parallel-group, pragmatic, single-centred, randomised controlled trial. An anticipated 122 adults, newly diagnosed with glaucoma (including ocular hypertension, suspected glaucoma and/or chronic open-angle glaucoma) will be recruited from a nurse-led ophthalmology outpatient clinic at a medium-sized NHS Trust. Participants will be randomly allocated to receive standard clinical care (control arm) or standard care plus a glaucoma personal record, detailing the current state of their condition (interventional arm). Participant assessments are designed to test whether provision of a glaucoma personal record 1) improves patient knowledge of glaucoma and 2) contributes to improvements in clinical outcomes, i.e. delay of visual field loss. The primary outcome measure is better client knowledge of glaucoma at the 9–12 month follow-up visit. Secondary outcome measures include the rate of visual field loss and patient-reported outcome measures on visual function (National Eye Institute VFQ – 25) measured at baseline, 9–12 months, 24 months and 36 months. Estimating a 20 % drop-out rate, the study will have 90 % power to detect a mean two-point difference in glaucoma knowledge score between groups at 5 % significance - based on two-sided Mann–Whitney *U* test.

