### Sample size

The anticipated patient sample size of 122 will be recruited over a 12-month period. Power calculations for sample size, 90 % power and 5 % significance, based on two-sided Mann–Whitney *U* test for the primary outcome measure, patient knowledge of glaucoma. A priori power calculations, using GPower 3.1 software, result in the following sample sizes summarized in Table 2. The calculation also takes into account a 20 % drop-out rate over the initial 9–12-month follow-up period before patients return for their regular glaucoma follow-up and knowledge questionnaire visit.

**Table 2 Tab2:** Sample size calculation

Mean score control group (± SD)	Mean score intervention group (± SD)	Required total sample size, n
7 (3)	8 (3)	400 (200 per group)
7 (3)	9 (3)	122 (61 per group)
7 (3)	10 (3)	58 (29 per group)

*SD* standard deviation

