### Randomisation

Each participant will be assigned to the control or interventional arm by a pragmatic randomisation approach; there will be no stratification and randomisation will take place on a 1:1 ratio without blocking. Online freeware will be used to generate a random allocation sequence in advance of the recruitment period, seen only by the trial administrator (who will not be involved with data collection) [9]. Allocation concealment will be achieved using consecutively numbered, sealed, opaque envelopes prepared in advance of recruitment by the trial administrator. This will ensure the investigator is not aware of the allocation sequence in advance of randomization. Eligible subjects will be randomised and - if assigned to the intervention arm - presented with their glaucoma personal record by the CI immediately after written informed consent has been obtained. For overview of the study process, see Fig. 1.

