#### Tertiary outcome

Participants’ demographic data will be collected and analysed to compare the distribution between control and intervention groups in terms of: age, gender, postcode and highest level of education achieved. The latter two are of particular relevance as the study will assess self-education and disease awareness [15]. The control and intervention groups will also be stratified by disease diagnosis (OHT, SG and COAG), although the aforementioned primary and secondary outcome measures are based on collective data.

Other potential confounding factors that will be recorded for each participant are related to general eye health and the resulting management of the newly diagnosed glaucoma. It will be recorded if patients: have never worn glasses/lenses, wear glasses/lenses due to old age (reading and/or driving), wear glasses since childhood or early adulthood due to congenital visual defect. Note will also made whether patients are prescribed IOP-lowering eye drops or undergo a laser or surgical intervention during the study period.

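### Baseline characteristics are significance-tested between randomised arms with no stated use, while the fixed primary test leaves out education, which the article itself marks as relevant

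*Protocol article*

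**What the plan says.** All references are to the protocol article.

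- **Baseline comparison.** The Tertiary outcome section compares the two arms on four variables: age, gender, postcode and educational attainment. Of the last two, postcode and education, it says: "The latter two are of particular relevance as the study will assess self-education and disease awareness". The Data analysis section adds that "any differences in distribution (e.g. patient age, sex, level of education) will be analysed by applying one-way ANOVA or chi-squared test". Neither section says what follows from a significant result.
- **Primary analysis.** Average knowledge scores are compared between arms, and "Statistical significance will be assessed by applying the Mann–Whitney" *U* test. The test takes no covariates. The Tertiary outcome section adds that outcomes are analysed on pooled data, so diagnosis does not enter either.
- **Allocation.** Under Randomisation, "there will be no stratification and randomisation will take place on a 1:1 ratio without blocking". Allocation is concealed in sealed, opaque envelopes.
- **No baseline score.** The Consent section describes a post-test-only design, and the study timeline table shows knowledge measured only at the first follow-up visit.
- **Sizing.** According to the Abstract, "the study will have 90 % power to detect a mean two-point difference in glaucoma knowledge score between groups at 5 % significance".

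**The concern.** Two choices pull against each other. The plan tests whether the arms differ at baseline. With proper randomisation any such difference arises by chance, so the p-value answers a question whose answer is already known and says nothing about whether an imbalance matters for the knowledge score. Meanwhile a variable that the authors regard as bearing on the outcome is collected and then kept out of the primary comparison.

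The design offers no other protection. There are no strata or blocks to limit imbalance in education, and no baseline knowledge score to adjust for. With about 49 evaluable patients per arm, a chance difference in education would pass straight into the comparison of average scores. At stake are the precision of the primary result and how far it can be trusted if the arms happen to differ in education.

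**Working it through.** **Inputs**

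- Difference 2 points (7 versus 9), SD 3 in each arm: Sample size section, Table 2. Standardised difference 2/3 = 0.667.
- "90 % power and 5 % significance", two-sided: Sample size section.
- Planned total "122 (61 per group"), of which "The calculation also takes into account a 20 % drop-out rate". Evaluable: 61 × 0.8 = 48.8, about 49 per arm.
- R², the share of score variance explained by baseline covariates: not given. **Assumed**, with 0.10–0.20 as the main range and 0.30 as a more extreme case.

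**1. The plan's own figure**

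- Normal approximation: n = 2(1.960 + 1.282)² × 3²/2² = 47.3, so 48 per arm. 48/0.8 = 60 per arm, 120 in total.
- Exact t-test: 49 per arm, and 98/0.8 = 122.5.
- Mann–Whitney with the normal-theory efficiency 3/π: 51 per arm, and 51 × 1.2 = 61.2, so 61 per arm and 122 in total.

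The planned 122 is reproduced to within rounding and the choice of method. The trial reaches its target without adjustment, so no shortfall is being repaired.

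**2. False baseline imbalances**

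With k independent tests at 5%, P(at least one significant) = 1 − 0.95^k.

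- Four variables named under Tertiary outcome: 1 − 0.95⁴ = 18.5%.
- Three given as examples under Data analysis: 1 − 0.95³ = 14.3%.

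**3. Power at 49 evaluable per arm**

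Unadjusted, by normal approximation: Φ(2/(3√(2/49)) − 1.96) = Φ(3.30 − 1.96) = 91.0%. For the Mann–Whitney test with efficiency 3/π: 89.1%.

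Adjustment replaces the SD of 3 by 3√(1 − R²), which is worth a sample larger by 1/(1 − R²) − 1. The simulations used 20,000 runs per R², 98 patients, simple randomisation and one normally distributed covariate.

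| Assumed R² | Residual SD | Equivalent extra sample | ANCOVA power, normal approx. | Simulated Mann–Whitney | Simulated ANCOVA |
|---|---|---|---|---|---|
| 0.10 | 2.85 | 11% | 93.6% | 88% | 92% |
| 0.20 | 2.68 | 25% | 95.8% | 89% | 95% |
| 0.30 | 2.51 | 43% | 97.6% | 89% | 97% |

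**4. Type I error in the same simulations**

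- Overall, unadjusted Mann–Whitney: 5.1%, 4.7% and 5.0% at R² 0.10, 0.20 and 0.30. The test is valid.
- Only in runs where the covariate was imbalanced at p < 0.05 (about 5% of runs, so roughly 1,000 per estimate): about 9%, 13% and 23% unadjusted, against about 5%, 5% and 7% for ANCOVA.

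The nominal 5% is therefore an average over all allocations. It does not hold for the particular allocation in which a prognostic covariate is out of balance, whereas the adjusted analysis stays close to 5%.

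**The case against.** The strongest reply is that the primary test is sound and consistent with the plan. The score is described as ordinal, the trial was sized on the Mann–Whitney test, and the analysis uses it. Its 5% error rate already allows for chance imbalance, and the inflated rates appear only after conditioning on an imbalance. Adjustment is then a gain in efficiency of unknown size, because the article gives no R². **This stands** as a limit on severity, but it does not answer the loss of precision.

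The reply continues that a linear model suits this score poorly, since the maximum is 12 or 17 depending on whether drops are prescribed. It adds that the timing is awkward: the Trial status section reports 85% of the sample recruited, and the outcome assessor is not masked. **Both points bear on the form of the fix**: the choice of model must be open, and the change must be dated.

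Several stronger readings are tempting, and the documents do not support them:

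- *The unadjusted primary test is invalid or biased.* Its overall type I error is about 5% and its power 89–91%.
- *Age was collected because it bears on knowledge.* The remark on relevance covers postcode and education only. Age is merely compared.
- *The baseline data are never used, or post hoc adjustment is planned.* The article states no use, but the full protocol and any SAP are not shown, and nothing makes adjustment depend on a baseline p-value.
- *More variables are tested, so the false-alarm rate is higher.* Six variables would give 1 − 0.95⁶ = 26.5%, but the article names four for the comparison between arms.
- *The absence of a confidence interval is itself a fault.* An article may leave that to the SAP.

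**Conclusion.** The point holds as a recommended improvement to a stated analysis and does not correct an invalid test. The baseline significance tests serve no purpose under concealed randomisation and should go. If the four variables are independent, they carry an 18.5% chance of at least one false signal. The primary comparison forgoes precision that is available at almost no cost: power of about 89% would become about 92–95% at 49 per arm. It also leaves the result exposed to chance imbalance in education.

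The size of the gain rests on an assumed R² of 0.10–0.20, a single covariate with a linear effect, SD 3 and 20% drop-out. If education explains little of the score, the gain shrinks towards nothing, but so does the cost of adjusting.

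**What to change.** 1. Remove the ANOVA and chi-squared tests of baseline variables and tabulate the arms descriptively.
2. Before the outcome data are analysed, prespecify the primary comparison of the knowledge score adjusted for education level, whatever imbalance is observed. Age is an optional further baseline covariate. Choose one model: ANCOVA, reporting the adjusted mean difference with its 95% CI, or a proportional-odds model, reporting an odds ratio with its 95% CI. ANCOVA speaks directly to the two-point difference; the proportional-odds model respects the ordinal scale.
3. Do not adjust for drops, laser or surgery during the study. They arise after randomisation.
4. Keep the unadjusted Mann–Whitney test as a sensitivity analysis.

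**Cost.** The change is to wording only, since education and age are already collected. There are two small downsides. One is a model assumption for an ordinal score with two possible maxima, which the retained rank test helps to check. The other is a departure, while recruitment is under way, from the test on which the trial was sized. That change should be documented and dated, with a statement of who had seen outcome data by then.

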#### Secondary outcomes

The secondary, longer-term, outcome measure is rate of visual field loss. In line with clinical practice, visual field loss will be measured at least annually (more frequently if there is a clinical indication). The relative visual loss rates between control and intervention groups will also be measured annually. Visual field testing will be performed by standard automated perimetry (SAP) using the Humphrey Central 24–2 programme. The Humphrey perimeter provides print-outs with statistical analyses of single field-test results, including numerical indices of reliability, and deviation from the norm of age-matched visual field analyses. The visual field indices used to identify progression of visual field loss will be mean deviation (MD) from the mean. MD represents the average difference between normal age-corrected sensitivity values and the subjects’ measured values at all test points. The rate of progression of visual field loss will be measured by linear regression analysis of the MD from the mean, expressed in decibels per year (or the newer visual field index, which was not available at the start of this study).

A simple measure was selected for use in this trial. However, there are challenges to using visual field analyses to detect progression. The test is subject to variability in performance, even for the same patient. Modern perimetry attempts to reduce sources of error in, for example, reduced test time, continuous gaze/fixation monitoring. The role of the operator is crucial in assisting patients to perform the test as accurately as possible [13]. All visual field testing will be undertaken by the CI to reduce inter-assessor variability.

Trend analyses to quantify rate of visual field loss require at least five tests to detect progression. This means relatively frequent testing in the first 2 years following diagnosis, especially if patients initially present with loss. The European Glaucoma Society (EGS) suggest three tests a year in the first 2 years. As such, this secondary outcome measure will take approximately 2–5 years to establish. The MD score will be documented in the ‘glaucoma personal record’ for the intervention group, and obtained from standard medical records for the control group.

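### Visual-field outcome is defined as an MD slope in dB per year, but the planned analysis compares only baseline and 36-month averages and estimates no rate

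*Protocol article*

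**What the plan says.** The abstract of the protocol article (Methods/Design) states: "Secondary outcome measures include the rate of visual field loss". The Objective section also aims at a lower rate of loss. Secondary outcomes repeats this, "The secondary, longer-term, outcome measure is rate of visual field loss", and says how the rate is obtained: "measured by linear regression analysis of the MD from the mean, expressed in decibels per year". It adds that loss rates in the two arms will be set against each other every year, and it allows an alternative index: "or the newer visual field index, which was not available at the start of this study". It also remarks: "Trend analyses to quantify rate of visual field loss require at least five tests to detect progression".

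Data analysis describes something else: "average measurements for baseline visit and the final visit at 36 months will be compared within each group (control and intervention respectively". The sentence then adds a comparison between the two groups. The test depends on a pre-test: "Depending on distribution of the data, determined by Shapiro-Wilk test, the paired" *t* test or the Wilcoxon test is used within arms, and the *t* test or Mann–Whitney *U* test between arms.

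The timeline table lists clinical parameters at baseline, 9–12, 24 and 36 months. Secondary outcomes says fields are taken at least once a year, and more often when clinically indicated.

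**The concern.** The article commits to two different quantities for one outcome: a per-year slope from all fields, and a contrast of averages at two visits. This is not detail left to an unseen analysis plan, because the Data analysis section does name a method and that method is not the one the outcome definition calls for.

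Three things are at stake:
- The reported result may not be in dB per year, and fields between baseline and 36 months would not contribute to it.
- Within-arm tests invite the reading that one arm progressed and the other did not, which is not evidence about the record.
- The index (MD or visual field index) and the variable in the between-arm test are not fixed in advance. The Discussion says the only outcome assessor is unmasked.

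**Working it through.** The article gives no effect size, SD or power for this outcome, so there is no figure of its own to reproduce. The check is a comparison of the text followed by illustrations on stated assumptions.

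**1. The two sections side by side.**

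| | Secondary outcomes | Data analysis |
|---|---|---|
| Quantity | rate of loss | averages at two visits |
| Unit | dB per year | none stated |
| Fields used | regression over the fields | baseline and 36 months |
| Between-arm contrast | relative loss rates, yearly | *t* or Mann–Whitney, variable not named |
| Within-arm tests | none | paired *t* or Wilcoxon |
| Index | MD, or visual field index | not named |

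**2. Precision of a slope against a two-visit rate.** Assume linear decline and independent error of variance σ² per field.
- Slope: variance = σ²/Sxx, where Sxx = Σ(tᵢ − t̄)².
- Two-visit rate, (36-month − baseline)/3: variance = 2σ²/3² = 0.222σ².
- Tabulated visits at 0, 0.875 (middle of 9–12 months), 2 and 3 years: t̄ = 5.875/4 = 1.469; Sxx = 13.766 − 4 × 1.469² = 5.137; variance = 0.195σ².
- Ratio = 0.195/0.222 = 0.876, so the slope has about 12% lower variance. The two-visit standard error is larger by √(1/0.876) = 1.068, about 7%.
- With the second visit at 9 or 12 months the ratio is 0.850 or 0.900, so the reduction lies between 10% and 15%.

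At a given visit timing this is an upper limit. If true slopes vary between patients with variance τ², that term adds to both: (τ² + 0.195σ²)/(τ² + 0.222σ²). If τ² = 0.222σ² (an assumption), the ratio is 0.417/0.444 = 0.94.

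With extra fields the gap widens. Five fields at 0, 0.5, 1, 2 and 3 years (assumed) give a ratio of 0.776. Three a year for two years plus month 36 give 0.151/0.222 = 0.681. The article cites three tests a year over two years as a society's suggestion; it does not adopt that schedule.

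**3. Which variable the between-arm test uses.** With equal variance at both visits and correlation ρ between them, var(change)/var(36-month value) = 2(1 − ρ). The article gives no ρ. For ρ = 0.5, 0.7 and 0.9 the ratio is 1.0, 0.6 and 0.2. This unstated choice can matter more than slope against change.

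**4. Within-arm tests.** Suppose both arms decline equally and each within-arm test has power p. The chance that exactly one arm is significant is 2p(1 − p). Take 48 patients per arm (61 × 0.8 = 48.8; an assumption, since the article's 20% drop-out covers only the first 9–12 months).

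| Assumed standardised change | Within-arm power | Exactly one arm significant |
|---|---|---|
| 0.2 | 0.274 | 0.40 |
| 0.3 | 0.530 | 0.50 |
| 0.4 | 0.775 | 0.35 |
| 0.5 | 0.924 | 0.14 |

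A split verdict between the arms is therefore common when the record does nothing.

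**The case against.** The strongest reply is that the plan is less broken than it looks. Secondary outcomes does specify a regression and does promise a comparison of loss rates between arms. The between-arm sentence in Data analysis names no variable, so it could be applied to rates. Under linear decline, change divided by three has the same expectation as the slope. All of this stands, and it limits the point.

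Four stronger readings are tempting but not supported:
- **That the trial cannot report its stated outcome.** The MD values will exist and the outcome section describes the regression. The fault is that the two sections disagree.
- **That only within-arm tests are planned.** A between-arm test is planned. Split within-arm results mislead only if they are read in its place.
- **That four tabulated visits breach the article's own five-test minimum.** The five tests are tied to detecting progression. They are not made a condition for including a patient in a comparison of mean rates, and the same section foresees denser testing early on.
- **That well-measured patients would be those suspected of worsening.** The article speaks of clinical indication and links denser testing especially to patients who present with loss. Worsening is an inference.

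The Shapiro-Wilk rule can be defended as a stated rule rather than an open choice. That is fair, but it still lets the data decide between a comparison of means and a rank test, and neither is tied to a rate in dB per year.

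**Conclusion.** The contradiction is real and should be removed. The outcome is a rate in dB per year, and the stated analysis does not produce one. The cost in precision is modest on the four tabulated visits: about 12% in variance at mid-window, 10–15% across the window, and less once patients' true slopes differ. It is larger if extra fields are taken. These figures rest on linear decline and independent, equal errors. The split-verdict probabilities of 14% to 50% rest on assumed effect sizes and an assumed 48 patients per arm.

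The outcome is secondary. The sample size and null hypothesis concern knowledge only, so the primary conclusion is untouched. This is a should-fix point and does not threaten the trial.

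**What to change.** Make the Data analysis section match Secondary outcomes:
- Name MD as the single index and remove the visual field index alternative.
- Make the between-arm difference in MD slope (dB per year, 95% CI) the one inferential result. One suitable form is the arm-by-time term of a linear mixed model on all MD values by actual test date, with random intercept and slope per patient. Include patients with fewer than five fields.
- Drop the Shapiro-Wilk switch and make within-arm comparisons descriptive only.

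Comparing per-patient slopes, or redefining the outcome as baseline-adjusted 36-month MD, would also reconcile the text. The second gives up the rate that the objective names.

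The cost is wording and slightly more analysis work, with no new data. One caveat remains to be reported: extra fields are clinically triggered, and the mixed model does not by itself remove that concern. Recruitment began in June 2013, so no 36-month field falls due before June 2016. The change should be dated before those data are seen.

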### Intervention description

Both groups will have exposure to current educational resources and materials presented at diagnosis, as is standard clinical practice. This may include an enlarged model of the eye, ocular anatomy posters, ocular coherence tomography sample scans, images of healthy and damaged optic nerve heads, examples of normal visual field tests and those showing glaucomatous loss, and a glaucoma information leaflet to take away with them. The chief investigator’s contact number will also be provided, as would be standard in her capacity as clinical nurse specialist in ophthalmology.

Those participants allocated to the interventional arm will, in addition to standard clinical care, be provided with their own ‘glaucoma personal record’ (Additional file 1), which will be personalised to document the current state of each participants’ glaucoma diagnosis and utilised during ophthalmologic review. Both groups of participants will be asked to complete the National Eye Institute Visual Functioning Questionnaire – 25 (VFQ-25) to gain an insight into patients’ perceptions about the impact that glaucoma may have on their daily living. The ‘glaucoma personal record’ will be administered to those participants randomised to receive the intervention by the CI immediately after the informed consent process has been completed.

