### Outcome measures

#### Primary outcome

The primary outcome measure is client knowledge of glaucoma, quantified using a validated researcher-conducted survey at 6–12 months post-recruitment [8], see Table 3. This survey and scoring system was used, and validated by ophthalmic colleagues in 2009/2010 “to establish the impact of educational support on clients’ knowledge of glaucoma and adherence, in preparation for a further interventional study” [9]. It provides an ordinal score of participants’ knowledge. The primary outcome measure is therefore the degree of understanding and knowledge retention of their OHT, SG, or COAG in the interventional group compared with the control group. Patients requiring ocular antihypertensive treatment at first presentation are eligible for inclusion in this trial; the total knowledge score achievable is either 12 for those not prescribed antihypertensive drops, or 17 for those prescribed eye drops during the course of the study. The survey will be administered by the CI when participants attend a ‘glaucoma review’ outpatient clinic between 6 and 12 months post-recruitment.

**Table 4 Tab3:** Overview of study timeline and outcome measures

Baseline	Baseline	9–12 months	24 months	36 months
Patient knowledge		X		
Patient perspective (VFQ-25)	X	X	X	X
Clinical parameters	X	X	X	X

*VFQ-25* National Eye Institute Visual Functioning Questionnaire – 25

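### VFQ-25 is tested within each arm and by an unadjusted between-arm Mann–Whitney test, although a baseline score is collected; one baseline-adjusted comparison would answer the question more precisely

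*Protocol article*

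**What the plan says.** The Abstract lists VFQ-25 as a secondary outcome "measured at baseline, 9–12 months, 24 months and 36 months". The timeline table gives the same four visits; the Secondary outcomes section puts the first follow-up at 6–12 months instead.

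The Data analysis section says that the "patient-related outcome measure VFQ-25 - will be presented as average scores", and then: "Any statistical differences will be assessed by Wilcoxon test within each group and Mann–Whitney" U test between groups. It names no covariate. It does not say which of the three follow-up visits the between-arm test uses, or whether follow-up or change scores are compared.

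On the order of events at the first visit, the Intervention description says "Both groups of participants will be asked to complete the National Eye Institute Visual Functioning Questionnaire" but does not place this relative to consent, randomisation or handover. The Randomisation section says that intervention participants are "presented with their glaucoma personal record by the CI immediately after written informed consent has been obtained".

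The only power statement is "90 % power and 5 % significance, based on two-sided Mann–Whitney" U test, and it concerns the knowledge score. VFQ-25 has no stated standard deviation, target difference or power.

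**The concern.** The trial asks whether the record does better than standard care. Randomisation protects the contrast between arms; a test of change within one arm also picks up time, treatment, learning and regression to the mean. Reporting a Wilcoxon p-value for each arm invites the reading that the record worked because one arm changed significantly and the other did not, which can easily happen when the arms do not differ.

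The between-arm test does address the question. However, the trial already collects each participant's starting score, and the stated test makes no adjustment for it. In a trial of 122, sized on another outcome, that precision matters. With three follow-up visits and two possible quantities, the wording also admits 3 × 2 = 6 different between-arm tests.

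**Working it through.** **Plan's own figure.** There is none for VFQ-25. The stated total for the knowledge score (7 v 9, SD 3, so d = 2/3; two-sided 5%; 90% power) reproduces closely. A t test needs 49 per arm, and 98/0.8 = 122.5. Mann–Whitney with asymptotic relative efficiency 3/π needs 51 per arm, and 51 × 1.2 = 61.2. With 61 × 0.8 = 48.8, say 49, completers per arm, Mann–Whitney power is 89.7%. I use 49 per arm below. The 20% loss applies only to 9–12 months and the article gives no figure for 36 months, so 49 may be optimistic there.

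**Within-arm tests.** Let both arms have the same true change and each within-arm test have power p. The arms are independent, so P(exactly one significant) = 2p(1−p):
- p = 0.80: 2 × 0.80 × 0.20 = 0.32
- p = 0.50: 2 × 0.50 × 0.50 = 0.50, the maximum
- p = 0.30: 2 × 0.30 × 0.70 = 0.42
- no change in either arm, p = 0.05: 2 × 0.05 × 0.95 = 0.095

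**Precision of the between-arm comparison.** The article gives no baseline to follow-up correlation r, so a range is assumed. Relative to comparing follow-up means, the variance of the arm difference is multiplied by 1 − r² with baseline adjustment (ANCOVA) and by 2(1 − r) with change scores.

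| r (assumed) | ANCOVA, 1 − r² | Reduction | Change score, 2(1 − r) |
|---|---|---|---|
| 0.3 | 0.91 | 9% | 1.40 |
| 0.5 | 0.75 | 25% | 1.00 |
| 0.7 | 0.51 | 49% | 0.60 |
| 0.8 | 0.36 | 64% | 0.40 |

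**In terms of power.** For illustration take a true difference of 0.5 SD, 49 per arm and normal scores. Power = Φ(0.5 × √(n/2)/s − 1.96), where s is the square root of the factor above and n is 49 for ANCOVA or 49 × 3/π = 46.8 for Mann–Whitney.

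| r (assumed) | Mann–Whitney, follow-up | Mann–Whitney, change | ANCOVA |
|---|---|---|---|
| 0.3 | 67.7% | 53.3% | 73.7% |
| 0.5 | 67.7% | 67.7% | 81.5% |
| 0.7 | 67.7% | 87.7% | 93.4% |
| 0.8 | 67.7% | 96.9% | 98.5% |

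About two points of the ANCOVA advantage come from assuming normality: at r = 0 it would have Φ(0.5 × √24.5 − 1.96) = 69.7%. The rest comes from the baseline. Differences detectable with 90% power are 0.67 SD for Mann–Whitney on follow-up scores, against 0.63, 0.57, 0.47 and 0.39 SD for ANCOVA at the four correlations.

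**The case against.** A between-arm Mann–Whitney test is a valid analysis of a randomised comparison, and leaving out the baseline costs precision without introducing bias. VFQ-25 is secondary and has no power target. The visit, the quantity compared and the covariates are details that a statistical analysis plan commonly settles. The article also does not say that within-arm p-values will be used to claim an effect. The chance of discordant within-arm results is not the false-positive rate of the planned between-arm test, and 50% is its maximum. The correlations are assumed; at 0.3 the gain is modest. The factor 1 − r² compares linear estimators, and if scores are skewed a rank test may recover part of the difference.

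All of this stands, and it limits the point to one of efficiency and clarity. It does not remove it. The article fixes the two tests by name, and the within-arm one does not answer the trial's question.

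Two stronger readings are tempting. A reader might infer that the baseline is ignored altogether. The text does not support that: the within-arm Wilcoxon is a paired test and may use the baseline, and the between-arm test could be on change scores. That alternative would not settle the matter, since at correlations of 0.5 or below change scores are no more precise than follow-up scores.

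A reader might also infer that the intervention arm completes its baseline VFQ-25 after receiving the record, because the record is "administered to those participants randomised to receive the intervention by the CI immediately after the informed consent process has been completed". No sentence says so. Randomisation itself falls between consent and handover, so that wording does not exclude an intervening step, and the questionnaire is given no place in the sequence. The trial schema (Fig. 1), which may show the order, could not be consulted.

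**Conclusion.** The point holds as one about the choice of analysis for a secondary outcome. The within-arm tests do not assess the record's effect: with equal true change they disagree between arms in 32% of trials at 80% within-arm power and 50% at 50%. The between-arm test is valid but less precise than the collected data allow, by 9%, 25% or 64% of the variance at correlations of 0.3, 0.5 or 0.8. Those figures rest on assumed correlations and a linear comparison; the power figures also assume normal scores and 49 completers per arm.

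It is not established that the baseline follows handover. The order is unstated. It matters because participants are not masked, and a score given after seeing the record could be influenced by allocation. That would weaken it as a covariate, as a reference for change scores and as the first measurement in the within-arm tests.

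**What to change.** 1. Make one baseline-adjusted between-arm comparison the VFQ-25 analysis: ANCOVA at 36 months, or a repeated-measures model of the three follow-up scores with baseline VFQ-25, arm, time and arm-by-time. If scores are clearly skewed, use a rank-based or bootstrap version of the same comparison.
2. Report the arm difference at 36 months with its 95% confidence interval.
3. Present within-arm changes descriptively, without tests.
4. Before using the baseline as a covariate, confirm from the full protocol, the schema or clinic procedure that it was completed before the record was handed over, and state the order. If this cannot be confirmed, lead with the unadjusted comparison of 36-month scores and give the adjusted one as a sensitivity analysis.

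The cost is revised analysis wording, some added model assumptions and slightly more analysis work. The analysis itself needs no new outcome data or visits. The Trial status section reports 85% of the sample recruited, so a clarified visit order can reach only about 0.15 × 122 ≈ 18 further participants. For the rest the order has to be established from existing procedure or records, and the article does not say that it was recorded.
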